### 4.5. Study Scheme

#### 4.5.1. Module I

**Initial Visit: Prehabilitation—Patient Admission and Initial Assessment (21 +/− 7 days before surgery)**

The initial visit includes presenting the potential participant with verbal and written information about the proposed study, providing a copy of the “Information for Study Participants” document, and providing a copy of a written informed consent form for participation in the study. At this stage, the participant should be fully informed by the Investigator about the study’s nature and schedule and their rights and responsibilities and receive detailed information from the Investigator on all relevant aspects, including the potential risks and benefits of participation.

Because eligibility can be confirmed without additional diagnostic testing solely for research purposes, the initial eligibility assessment may be combined with Visit 1. Participants who need additional time to review the informed consent form and participant information document may complete consent at a subsequent visit before any study-specific procedure is performed.

Every participant will be informed of their right to withdraw from the study at any stage without the need to provide a reason. Before any study procedure is initiated, the process of obtaining informed consent from the participant must be fully completed.**Visit 1: Following Completion of Informed Consent Process**

1. The participant’s completion of the informed consent procedure will be documented, and the randomization process (Principal Investigator, Investigator) will be completed.

2. The Investigator will confirm in writing that the participant meets the inclusion/exclusion criteria on the designated study form.

3. Demographic and medical history interviews: The participant will respond to questions according to the study questionnaire, covering topics such as lifestyle habits, family history of cancer, and level of independence.

4. The American Society of Anesthesiologists (ASA) classification will be used to evaluate surgical risk related to serious complications or mortality during or after anesthesia.

5. A quality-of-life assessment using the SF-36 questionnaire will be provided to the patient, enabling them to self-evaluate their health status.

6. Pain intensity will be determined via the Numeric Rating Scale (NRS).

7. Physical functioning will be assessed via the Zubrod–ECOG–WHO scale (Eastern Cooperative Oncology Group), which is commonly used to evaluate the general condition and quality of life of cancer patients and in geriatrics, psychiatry, and chronic diseases.

8. The Charlson Comorbidity Index (CCI) will be used to estimate the 10-year survival probability in patients with multiple comorbidities.

9. Venous thromboembolism risk will be evaluated using the Caprini scale.

10. An assessment using the G8 scale for geriatric screening will be performed.

11. For older adults, a health status assessment will be conducted using the Vulnerable Elders Survey (VES).

12. The participant’s need for specialist consultations will be assessed (coordinated under SOSNP).

13. Blood will be collected for laboratory testing (CBC, electrolytes, albumin, cholesterol, total protein, triglycerides, TSH, FT3, FT4, iron, vitamin D3, AST, ALT, and GGTP) and biobanking. At the 4th Military Clinical Hospital, the protocol-defined allostatic load panel will additionally be assessed.

14. A nutritional assessment, including anthropometric measurements (BMI, WHR), a nutritional status evaluation using bioelectrical impedance analysis (BIA), and a clinical dietitian interview will be conducted.

15. A psychological evaluation will be conducted (HADS, MMSE).

16. Physiotherapy assessment: Grip strength (dynamometer), a six-minute walk test (6MWT), a FEV-1 test, and a sit-to-stand test (using a wristband) will be conducted.

17. A participant activity assessment will be conducted using a smart wristband. A mobile app will be installed on the participant’s smartphone that will store and cycle data from the wristband, such as step count, sleep duration, and heart rate. Training will be provided on wristband usage, measurement techniques, app functionality, and technical support.

18. Clinical pharmacist assessment: A medication review will be conducted.

19. Addiction-related re-education will be conducted (if applicable).

The collected data will serve as a baseline for evaluating study endpoints (initial assessments).**Visit 2: Summary Prehabilitation Visit (Hospital Admission Day For Surgery)**

1. Health Status Update: A targeted interview will be conducted to assess any changes in the participant’s general health status since the first visit. A visit form will be completed, and scales will be reassessed for comparison with Visit 1 results.

2. Specialist Consultation Needs: An assessment will be conducted to identify any specialist consultation needs of the participant.

3. Treatment Plan Discussion: The treatment plan, including the surgery date and discharge schedule, will be discussed with the patient and caregiver (if applicable).

4. Nutritional Assessment: A dietary evaluation, anthropometric measurements (BMI, WHR), and a nutritional status assessment will be conducted using bioelectrical impedance analysis (BIA) and a clinical dietitian interview.

5. Psychological Assessment: A psychological assessment will be performed using the HADS.

6. Physical Therapy Assessment: Physical functionality will be evaluated through grip strength testing (with a dynamometer), the 6MWT, an FEV-1 test, and a sit-to-stand test with a smart wristband.

7. Activity Level Evaluation: The participant’s activity level will be assessed through data analysis using the data from the dedicated mobile application.

8. Clinical Pharmacist Evaluation: An assessment by a clinical pharmacist will be conducted.

9. Substance Cessation Assessment: An evaluation related to substance cessation will be conducted.

10. Medical Laboratory Diagnostics: Blood tests will include a CBC and measurement of electrolytes, albumin, cholesterol, total protein, triglycerides, TSH, FT3, FT4, iron, vitamin D3, AST, ALT, and GGTP. At the 4th Military Clinical Hospital, the protocol-defined allostatic load panel will additionally be assessed.

11. Participant Satisfaction Survey: A satisfaction survey will be conducted to assess the participant’s experience with the prehabilitation program.

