## 2. Materials and Methods

### 2.1. Study Design

This is a prospective, two-center, two-arm, parallel-group randomized controlled study evaluating the RESET perioperative care pathway in two predefined surgical populations. Participants who provide written informed consent and meet the eligibility criteria are randomized in a 9:1 ratio to the RESET intervention or standard-care control arm. Exploratory analyses may additionally use routinely collected clinical outcomes from a naturally formed group of eligible patients who do not participate, as prespecified in the approved protocol. The study was approved by the Bioethics Committee at the Lower Silesian Medical Chamber in Wroclaw (approval No. 33/BNBO/2025, 12 November 2025). Protocol version 1.2, dated 27 March 2026, was developed in accordance with the SPIRIT 2013 Statement (Additional File 1) [33]. The study is being conducted at the Regional Specialist Hospital in Wroclaw and the 4th Military Clinical Hospital with Polyclinic in Wroclaw.

The primary treatment effect of interest is the effect of assignment to the RESET pathway, compared with standard perioperative care, on each of the three primary outcomes: postoperative complications, prolonged index hospitalization, and 30-day unplanned hospital readmission. Each outcome will be evaluated separately within the oncology and non-oncology populations, yielding six primary hypothesis tests. Primary analyses will follow the intention-to-treat principle, with per-protocol analyses used as supportive assessments. The confirmatory decision rule and multiplicity control across all six outcome-by-population tests are specified in the Statistical Methods section of this paper. The overall study design and participant flow are presented in Figure 1.

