#### 4.2.1. Randomization

After written informed consent and confirmation of eligibility, each participant is assigned a unique study identification number. Randomization is performed centrally through a secure web-based system using a computer-generated dynamic allocation procedure based on a biased-coin algorithm. The procedure monitors cumulative allocation within each predefined clinical population and adjusts assignment probabilities as needed to maintain the protocol-defined 9:1 intervention-to-control ratio. Allocation is generated only after participant enrollment and eligibility confirmation and cannot be predicted or modified by Recruiting Investigators.

The unequal 9:1 allocation was chosen a priori for ethical and implementation reasons, principally to allow the greatest possible proportion of seriously ill surgical patients—particularly those undergoing oncological surgery—to receive the low-risk, multimodal RESET pathway while retaining a randomized standard-care comparator. The lower statistical efficiency associated with the smaller control group was taken into account in the approved sample-size planning described below. Under the simplifying assumption of equal outcome variances and a fixed total sample size, a 9:1 allocation has approximately 36% of the statistical efficiency of a 1:1 allocation for a simple two-group contrast (approximately 2.78-fold higher variance and 1.67-fold higher standard error). The substantially larger total recruitment target and prespecified covariate-adjusted analyses improve precision but do not eliminate this intrinsic efficiency penalty.

Randomization is conducted separately within the oncology and non-oncology populations. Allocation data are kept separate from participant-identifying and outcome data. No fixed block sizes or additional stratification factors are used beyond the separation of the two predefined clinical populations.

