#### 4.5.3. Module III

**Postoperative Recovery (From the first day after the surgical procedure)**

Surgical Procedure and Hospitalization Assessment:Health Assessment: Regular monitoring of health parameters and treatment progress;Registration of the ICD-10 and ICD-9 procedure codes;Clavien–Dindo classification for complications;Evaluation of perioperative pharmacotherapy;Registration of anesthesia type;Monitoring of postanesthesia complications;Wound healing assessment via the VAS scale.Enhanced Recovery Protocol (early patient mobilization, bedside rehabilitation, gradual physical activation, nonstandard dietary management, additional rehabilitation support).Daily Red to Green assessment.Evaluation of family communication needs.The patient’s stay in the ward will adhere to the SAFER Patient Flow Bundle.

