Each of the three binary primary outcomes—prolonged index hospitalization, unplanned hospital readmission within 30 days after discharge, and at least one postoperative complication within 30 days after surgery—will be analyzed using logistic regression. Numbers and proportions of events will be reported for each randomized group together with treatment-effect estimates and confidence intervals.

Adjusted analyses will use a parsimonious set of baseline factors with clear prognostic relevance—age, sex, study site, study year, ASA class, Charlson Comorbidity Index, and broad surgical-procedure category—subject to final prospective specification in the statistical analysis plan. Unadjusted randomized comparisons will also be reported. Measures of adherence or intervention exposure recorded after randomization will not be used to adjust the principal treatment-effect models.

Repeated outcomes will be analyzed primarily using mixed-effects models appropriate to the measurement scale. Continuous repeated outcomes will be assessed with linear mixed-effects models, and binary, ordinal, or count repeated outcomes with generalized linear mixed-effects models using an appropriate link function. Models will include randomized group, assessment time point, and the group-by-time interaction, with a participant-level random intercept to account for within-participant correlation. Baseline handling, the covariance structure, any random slopes, the treatment of study site, and any additional prespecified prognostic covariates will be defined in the SAP before treatment effects are examined. Repeated-measures ANCOVA will be restricted to supportive or sensitivity analyses.

Effect estimates will be reported with confidence intervals in addition to *p* values. The protocol-defined two-sided α = 0.01 threshold will be retained as the nominal design threshold, and principal primary-effect estimates will be accompanied by 99% confidence intervals. Consistent with the protocol, nominal *p* values between 0.01 and 0.05 may be described as exploratory. For the six primary hypotheses, however, confirmatory status will be determined by the multiplicity-adjusted decision rule below; any primary result that does not satisfy that rule will be considered non-confirmatory irrespective of its nominal *p* value.

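### The Visit 1 list randomizes before it confirms eligibility, contradicting the randomization section, and it leaves every baseline assessment until after allocation

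*Protocol article*

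**What the plan says.** The protocol article describes the order of events in several places.

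- **Section 4.5.1, Visit 1, item 1:** "completion of the informed consent procedure will be documented, and the randomization process (Principal Investigator, Investigator) will be completed".
- **Section 4.5.1, Visit 1, item 2:** "The Investigator will confirm in writing that the participant meets the inclusion/exclusion criteria on the designated study form".
- **Section 4.5.1, Visit 1, items 3 to 19:** history, ASA, SF-36, pain, performance status, Charlson index, blood tests, nutrition, HADS, grip strength, six-minute walk and others. The list closes by giving these data their role: "The collected data will serve as a baseline for evaluating study endpoints (initial assessments".
- **Section 2.1:** "Participants who provide written informed consent and meet the eligibility criteria are randomized in a 9:1 ratio".
- **Section 4.2.1:** "Allocation is generated only after participant enrollment and eligibility confirmation and cannot be predicted or modified by Recruiting Investigators".
- **Table 1:** the eligibility form, demographics and medical history stand above randomization. Laboratory, nutritional, psychological, physiotherapy and scale assessments stand below it. All are marked in the same Visit 1 column.

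Section 5.2 compares change from the Visit 1 values between arms. Section 5.6 names the covariates for the adjusted primary analyses: "age, sex, study site, study year, ASA class, Charlson Comorbidity Index, and broad surgical-procedure category". Section 4.2.2 says that staff who deliver RESET know the allocation. It promises masking, where feasible, to outcome assessors and data analysts, and it does not mention whoever makes the baseline assessments.

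**The concern.** Two separate things are at stake.

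The first is a conflict over eligibility. A site that follows the Visit 1 list would allocate a participant before signing off eligibility; a site that follows section 4.2.1 would not. With two centers recruiting, the order should not depend on which section the staff read.

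The second is the timing of baseline. A measurement taken once the arm is known is no longer protected by randomization. ASA class is a judgement, the Charlson index depends on how thoroughly comorbidity is sought, and grip strength and the six-minute walk depend on effort and encouragement. SF-36, HADS and pain are self-reported. If any of these is recorded differently by arm, the difference passes into the change-from-baseline comparisons and, for ASA and Charlson, into the adjusted primary models.

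**Working it through.** The plan gives no figure to reproduce. The check sets the sections side by side.

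**1. Eligibility against allocation.** Section 2.1 puts eligibility first. Section 4.2.1 does so twice, at its opening and in the sentence quoted above. Visit 1 puts randomization at item 1 and eligibility at item 2. Section 4.5.1 also allows that "the initial eligibility assessment may be combined with Visit 1", so an eligibility check before Visit 1 cannot be taken for granted. Table 1 favors eligibility first by row order, but every row concerned carries its mark in the same visit column, so the table fixes no order within the visit. Result: a contradiction that nothing in the text resolves.

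**2. Baseline against allocation.** In the list, items 3 to 19 all come after item 1. Section 4.2.1 does not say when baseline data are collected, so there is nothing for the list to contradict. Table 1 does not place the physiotherapy, psychological, nutritional or scale assessments ahead of randomization either. Result: as written, baseline follows allocation, and no other section says otherwise.

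**3. Who could know the arm at baseline.** Section 4.4 gives the prehabilitation team as physician, dietitian, physiotherapist, psychologist, pharmacist and nurse coordinator. Visit 1 calls for dietitian, psychological, physiotherapy and pharmacist assessments. Section 4.3 describes the same walk, grip, FEV1 and sit-to-stand tests as part of the physical activity intervention. The professions overlap. The article does not say that the same individuals do both jobs, nor does it say that they are kept apart.

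**4. Where an influenced baseline would go.**
- Change outcomes: change = follow-up − baseline. If the baseline of one arm is recorded lower by an amount d, for reasons of allocation alone, the between-arm difference in change shifts by d even when follow-up is measured without error. If baseline enters as a covariate with slope b, the shift is b × d. Section 5.6 leaves baseline handling to the SAP, so either form is possible. The article gives no basis for a value of d.
- Adjusted primary models: 3 outcomes × 2 populations = 6 models. Of the seven covariates, ASA and Charlson are scored at Visit 1 and are open to judgement or ascertainment. Age, sex, site, study year and broad procedure category are practically not open to influence by allocation.
- Unadjusted primary comparisons: these use no covariate and are not touched by this route.

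**The case against.** The strongest reply is that this is a drafting slip. The list is numbered but never called chronological. Item 2 is a form, and could record a check already made. Eligibility needs no extra testing, and the criteria are mostly objective. Two sections and the row order of Table 1 favor eligibility first. This stands as far as it goes: the document does not establish that the trial in practice randomizes first. It does not remove the conflict in the text.

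On baseline, participants are not told their arm, and at Visit 1 they have had little from which to infer it. Laboratory values are hard to influence, and Charlson rests largely on documented diagnoses. This also stands, and it is why the point is a risk and not a bias shown.

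Three stronger readings are tempting and not supported:

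- **Late eligibility checks will selectively deplete the small control arm.** Section 5.6 analyzes all randomized participants as assigned and names eligibility deviations only as a basis for the supportive per-protocol set. The document gives no rate of such losses, so any percentage would be invented.
- **The primary results are compromised.** Unadjusted comparisons are reported as well, and only two covariates are exposed.
- **The procedure-category covariate is measured after surgery.** Module III does list "Registration of the ICD-10 and ICD-9 procedure codes", but nothing ties the covariate to those codes. Section 5.6 calls it a baseline factor, subject to final specification in the SAP.

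**Conclusion.** The point holds in two parts of different strength. The order of eligibility and allocation in Visit 1 contradicts sections 2.1 and 4.2.1; this is plain from the text. Placing all baseline assessments after allocation is a design weakness. It follows from the order of the list, together with the absence of any stated masking for baseline assessors.

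Its reach is the judged, self-reported or effort-dependent measures among the change-from-baseline secondary outcomes, and ASA and Charlson in the six adjusted primary models. Its size cannot be estimated from the document. Any effect requires that the list is followed as written and that the arm is known to, or guessed by, someone who can influence the measurement. Neither is shown. Intention-to-treat and the unadjusted comparisons protect the primary results to a large extent; the change-from-baseline outcomes have no equivalent protection. The correction is worth making now because recruitment is under way and a baseline recorded after allocation cannot be retaken.

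**What to change.** Reconcile section 4.5.1 with section 4.2.1 by reordering Visit 1:

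1. Consent.
2. Written confirmation of eligibility.
3. Baseline assessments, at least ASA, Charlson and every measure used for change from baseline.
4. Release of allocation, as the last step.

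If some assessments cannot be done before allocation, state that the people making them are unaware of it. Arrange the rows of Table 1 to match.

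Establish from the dates and times on record which order has been followed so far. If any participants were assessed after allocation was known, flag them and add a sensitivity analysis of the primary outcomes that omits ASA and Charlson from the adjustment set. If none were, correcting the text is enough.

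The cost is a change to the visit procedure. Allocation becomes known slightly later on the same day, so RESET planning starts that much later. Sample size, endpoints and the multiplicity rule do not change.

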### 4.2. Exclusion Criteria

-Cancer diagnosis.

Up to 12,800 potentially eligible patients will be approached and screened. At the stage of offering participation, approximately 25–35% of eligible patients are expected to decline; a 30% non-participation rate is assumed for planning purposes. Individuals who decline will not undergo study procedures, although routinely available clinical outcomes may be used in prespecified exploratory comparisons where permitted. Approximately 8960 participants are therefore expected to provide consent and be randomized. Randomized participants are allocated to the RESET intervention (90%) or standard-care control arm (10%). Both randomized arms undergo the protocol-defined assessment schedule; only the intervention arm receives the coordinated RESET pathway.

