#### 4.2.2. Blinding

Because RESET is an individualized multidisciplinary care pathway, complete blinding is not feasible. In accordance with the approved study design and trial registration, participants are informed about study participation but are not explicitly told whether they have been allocated to the individualized RESET pathway or to standard perioperative care. Both groups undergo the same protocol-defined assessments, questionnaires, and activity monitoring. Some participants may nevertheless infer their allocation from the nature or intensity of care received; participant masking therefore refers to non-disclosure of randomized allocation rather than assurance that allocation cannot be recognized. Personnel delivering RESET are necessarily aware of allocation. Surgeons and other inpatient clinicians are not routinely informed of study allocation for research purposes, although information required for safe clinical care is never withheld. Outcome assessors and data analysts remain unaware of allocation whenever feasible. Allocation data are kept separate from outcome data, and the three primary outcomes are objective clinical endpoints.

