### 5.3. Study Conditions and Analytic Strategy

The study includes two clinical populations, oncology and non-oncology, each randomized to intervention or control. Prespecified exploratory analyses may additionally include a naturally formed non-participant comparison group for routinely available clinical outcomes. Repeated outcomes measured at two or more protocol-defined time points will be analyzed using models that account for within-participant change, between-group effects, and relevant covariates. Outcomes measured once will be analyzed using endpoint-appropriate regression models.

The analysis has two complementary tracks. The primary randomized track comprises randomized comparisons of the RESET and standard-care arms. A secondary exploratory track may compare routinely available outcomes—prolonged hospitalization, readmission, length of stay, and postoperative complications—with the non-participant group. Patient-reported and participant-specific outcomes, including multidomain health status, satisfaction, and adherence, will be analyzed only among consenting randomized participants.

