## Figures and Tables

**Figure 1 mps-09-00134-f001:**
[figure not shown]
Flowchart of patient enrollment and participation.

**Table 1 mps-09-00134-t001:** Schedule of activities.

Procedure/Activity	Module I—Visit 1 21 ± 7 Days Before Surgery	Module I—Visit 2 Hospital Admission	Module II Hospitalization and Discharge	Module III Postoperative Recovery	Module IV 30-Day Post-Surgery Period	Final Visit 30-Day Post-Surgery Follow-Up
Informed consent	**X**					
Inclusion/Exclusion Form	**X**					
Demographics	**X**					
Medical history	**X**					**X**
Randomization	**X**					
RESET intervention	**X**	**X**	**X**	**X**	**X**	
Physical exam	**X**	**X**	**X**	**X**	**X**	**X**
Medical Laboratory Diagnostics	**X**	**X**	**X**	**X**		**X**
Nutritional assessment	**X**	**X**				**X**
Psychological evaluation	**X**	**X**				**X**
Physiotherapy assessment	**X**	**X**				**X**
Clinical pharmacist assessment	**X**	**X**				**X**
Addiction-related re-education (if applicable)	**X**					
Installation of a mobile app + wristband	**X**					
Activity Level Evaluation		**X**				**X**
Medical Scales Assessment	**X**	**X**	**X**	**X**	**X**	**X**
Treatment plan discussion		**X**				
Participant Satisfaction Survey		**X**				**X**
SAFER Bundle		**X**	**X**	**X**	**X**	
Red to Green		**X**	**X**	**X**	**X**	
Early Mobilization Program				**X**		
Transitional Care Program					**X**	
Complete Visit Forms	**X**	**X**	**X**	**X**	**X**	**X**

**X**, scheduled protocol-defined activity or assessment.

**Table 2 mps-09-00134-t002:** Conservative endpoint-specific design-sensitivity benchmarks for the fixed 9:1 randomized design.

Population	Primary Outcome	Assumed Control Risk	Detectable RESET Risk	Absolute Reduction	Odds Ratio	Relative Reduction
Oncology	Prolonged index hospitalization	20.0%	12.4%	7.6 pp	0.57	38%
Oncology	30-day readmission	12.0%	6.2%	5.8 pp	0.49	48%
Oncology	Postoperative complications	30.0%	21.0%	9.0 pp	0.62	30%
Non-oncology	Prolonged index hospitalization	15.0%	6.7%	8.3 pp	0.41	55%
Non-oncology	30-day readmission	10.0%	3.5%	6.5 pp	0.33	65%
Non-oncology	Postoperative complications	25.0%	14.2%	10.8 pp	0.50	43%

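### The Visit 2 satisfaction survey is framed around a program that only RESET patients receive, so its answers as described cannot be compared between arms

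*Protocol article*

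**What the plan says.** Section 4.5.1 (Module I) lists the procedures for Visit 2, which takes place on the day of admission for surgery. Item 11 reads: "A satisfaction survey will be conducted to assess the participant’s experience with the prehabilitation program". Table 1 has a row "Participant Satisfaction Survey", marked at Visit 2 and at the final 30-day visit.

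On who receives what, the closing paragraph of section 4.2 says that "Both randomized arms undergo the protocol-defined assessment schedule" and that "only the intervention arm receives the coordinated RESET pathway". Section 4.2.2 (Blinding) adds: "Both groups undergo the same protocol-defined assessments, questionnaires, and activity monitoring". The same section says that participants "are not explicitly told whether they have been allocated to the individualized RESET pathway or to standard perioperative care".

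On analysis, section 5.2 lists satisfaction as the third secondary endpoint, measured with a dedicated questionnaire whose items are not shown. Section 5.3 says that participant-specific outcomes, "including multidomain health status, satisfaction, and adherence, will be analyzed only among consenting randomized participants". Sections 5.3 and 5.6 together state that outcomes measured at two or more time points are analyzed with models that contain randomized group, time point and their interaction.

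**The concern.** A question about experience with a program presupposes that the respondent had one. A control patient could leave it blank, rate the research assessments as though they were the program, or mark it down because nothing was received. A RESET patient answers about prehabilitation actually delivered. The two sets of answers would be summarized on one scale but would refer to different things, and no analysis can repair that afterwards.

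Two things are at stake. The first is whether a between-arm difference in satisfaction at Visit 2 can be interpreted. The second, and lesser, is whether a trial form that refers to the program gives patients a cue to their allocation before surgery and before the day-30 self-reports, including SF-36 and HADS.

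**Working it through.** The article gives no satisfaction score, scale or power figure, so there is nothing to reproduce. The check sets the statements side by side.

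1. **Do controls complete the survey?** Section 4.2 puts both arms on the assessment schedule, and section 4.2.2 gives both the same questionnaires. A satisfaction survey is a questionnaire, and no control version or exemption is stated. As written, they do.

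2. **Did controls have the program?** Section 4.2 says they do not receive the pathway. Section 4.4 adds that assessments and activity monitoring in controls serve research and are not part of comparator care. A control who rates the dietitian or physiotherapy assessment as the program is rating something the protocol does not count as care.

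3. **How many are affected?** Section 5.4 plans about 570 oncology and 320 non-oncology controls: 570 + 320 = 890. Of about 8960 randomized, 890 / 8960 = 9.9%, which is essentially the whole control arm. It is an upper figure, because some controls will not reach Visit 2.

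4. **Is a between-arm comparison planned?** No sentence commits to one for satisfaction specifically. But Table 1 schedules two measurements, section 5.3 keeps the outcome among randomized patients without restricting it to RESET, and sections 5.3 and 5.6 prescribe group and group-by-time terms for repeated outcomes. That is the stated default.

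5. **What does the default model estimate?** Code RESET as G = 1 and control as G = 0, day 30 as T = 1 and Visit 2 as T = 0, with mean score b0 + b1·G + b2·T + b3·G·T. Then:
   - control at Visit 2: b0
   - RESET at Visit 2: b0 + b1
   - control at day 30: b0 + b2
   - RESET at day 30: b0 + b1 + b2 + b3

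   So b1 is the arm difference at Visit 2, and b3 is the day-30 difference minus the Visit 2 difference. Both use the Visit 2 control mean b0, which is the mean of answers to a question that does not apply to those respondents. The day-30 difference, b1 + b3, does not depend on the Visit 2 means when data are complete. It is affected only if the day-30 form has the same problem, or if missing day-30 answers are informed by Visit 2 answers through the model. The article does not describe the content of the day-30 survey.

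6. **Which way would the error go?** Of the three possible control responses, only scoring non-receipt as dissatisfaction clearly favors RESET. Blanks and ratings of the assessments could push either way. The sign cannot be derived from the document.

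**The case against.** The strongest reply is that satisfaction was never meant to be compared. The secondary objectives in the Introduction use the verb compare for costs but only assess for satisfaction, and they pair satisfaction with adherence to the prehabilitation pathway. Section 5.2 announces between-arm comparisons for health status and costs but not for satisfaction. The section 5.3 sentence mainly separates these outcomes from the non-participant analysis, and it lists adherence, largely a RESET-arm measure, alongside satisfaction. This stands in part: a descriptive, RESET-only reading is possible. But the article does not state it, and section 4.2.2 and the repeated-outcome rules point the other way.

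It is also fair that Table 1 proves nothing about arms. None of its rows is split by arm, and rows such as the RESET intervention and transitional care are plainly not for controls. The point therefore rests on sections 4.2 and 4.2.2, not on the table.

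A reader might infer more, namely that the survey tells controls before surgery what they missed and so breaks the masking. The documents do not support that. Item 11 is a one-line summary of purpose, and the questions patients see are not shown. Section 4.5.1 requires patients to be fully informed of the nature of the study at consent, so the survey is unlikely to be how a control learns that a program exists. Controls undergo many of the same specialist assessments at visits labelled as prehabilitation and may take those to be the program. Section 4.2.2 defines masking only as not disclosing allocation and concedes that some will guess it from the care they receive. What remains is that program wording may be a cue, and one that is easy to avoid.

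A reader might also infer that the survey favors RESET by construction, or that all satisfaction data are compromised. The first does not follow from the possible responses, and item 11 describes only the Visit 2 survey.

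**Conclusion.** The point holds for the Visit 2 survey. As described, its control answers (up to about 890 patients) do not measure the same thing as RESET answers, so the Visit 2 arm difference and the group-by-time term for satisfaction would not be interpretable. This assumes that sections 4.2 and 4.2.2 mean what they say about shared questionnaires, that item 11 reflects the content of the form, and that the default repeated-outcome model is applied to satisfaction. The direction and size of any distortion are unknown, since no scale is given. Any effect on masking is a possibility and would bear mainly on satisfaction and the later patient-reported outcomes. The six confirmatory tests use objective clinical endpoints and are little affected. This is a secondary-outcome defect worth correcting while recruitment continues, not a threat to the main conclusions.

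**What to change.** At Visit 2, give both arms an identical survey with arm-neutral items on preparation for surgery, information, coordination and care received since enrolment, without naming prehabilitation or RESET. Confirm that the day-30 survey uses the same neutral items, and name these as the between-arm satisfaction outcome. Put any program-specific items on a separate form for RESET patients only and report them descriptively for that arm.

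The cost is a revised questionnaire and a minor amendment. Recruitment began in February 2026, so surveys already collected may not pool with the reworded version. Those answers would then need to be reported separately, and the number affected grows the longer the change is delayed.
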